# Dimensional changes of peri-implant tissue following immediate flapless implant placement and provisionalization with or without xenograft in the anterior maxilla: a study protocol for a randomized controlled trial

**DOI:** 10.1186/s13063-022-06918-1

**Published:** 2022-11-26

**Keywords:** Immediate implant, Dental implant, Bone graft, Dimensional change, Buccal gap, Cone beam computed tomography (CBCT)

## Abstract

**Background:**

Dental implant therapy requires the preservation of peri-implant tissue in the cosmetic zone. Various surgical procedures have been presented, including ridge preservation, flapless method, and quick provisionalization. The goal of this research was to assess the buccal bone dimensional changes following immediate flapless implant implantation in the front maxilla, with or without xenografting.

**Method and design:**

Thirty patients who meet the inclusion criteria and have maxillary teeth (numbers 14 to 24) are candidates for the immediate implant with immediate provisionalization. Participants will be assigned randomly to one of two groups: (1) an immediate implant with xenograft and (2) an immediate implant without bone grafting. For 3 months, the temporary prosthesis will be installed shortly before the final restoration. Following temporary prosthesis insertion and 6 months after surgery, a CBCT radiograph will be used to examine bone tissue. Soft tissue will be assessed at three points: baseline, 3 months, and 6 months following implant therapy. Patients’ satisfaction, implant failure, prosthesis failure, and complications will be assessed as secondary outcomes after 6 months.

**Discussion:**

The outcomes of this randomized clinical research will show if buccal bone augmentation with xenograft reduces vertical bone and gingiva recession. The findings and patient-reported outcomes will aid in the selection of therapy alternatives for implant treatment patients.

**Trial registration:**

Iranian Registry of Clinical Trials IRCT20211119053106N1. Registered on 6 December 2021 and Open Science Framework (OSF) on May 20, 2022. Registration DOI 10.17605/OSF.IO/VUGFQ.

## Introduction

### Background

Implant placement is one of the most widely recognized, successful, and dependable tooth replacement solutions. Faster protocols compared to conventional dental implant procedures have been developed because of increased patient desire for cosmetics and social activities. Non-functional loading techniques and immediate implant insertion in fresh extraction sockets have become common therapy, especially in the cosmetic zone [1–3]. Following tooth extraction, bone tissue loss (40% of height and 60% of width) [3] and soft tissue alterations may cause functional and cosmetic issues. Because of its thinness and the existence of bundle bone, the buccal plate is more prone to volume and size decrease. For bone volume maintenance, many procedures such as atraumatic tooth extraction, flapless treatment, and preservation of the residual ridge have been recommended [3]. Many advantages of immediate implant placement (implantation at the same time instantly after extraction into the extraction socket) have been addressed, including preservation of alveolar bone, improved implant durability, psychological benefits, and reduced treatment time for patients [3, 4]. The large buccal gap/surrounding the immediate implant might occasionally interfere with bone repair and osteointegration [5]. As a consequence, excessive bone and soft tissue recession are caused by bone volume decrease and bone defects due to the significant activity of osteoblasts. Previous investigations have shown that small gaps heal naturally without the need for repair [5–9]. There are still some disagreements, and some studies recommend bone grafting if the buccal gap is more than 2 mm horizontally. Others, on the other hand, claim that there is no meaningful difference between utilizing a bone transplant and not using one [5]. A few studies have looked at filling the buccal gap with bone grafting material to minimize bone resorption and gingival tissue height and thickness between the immediate implant and the residual buccal wall [7, 10].

### Objective and hypothesis

The main objective of the randomized control trials is to evaluate dimensional changes of buccal bone after immediate flapless implant placement and bone grafting (xenograft) in the esthetic zone with a buccal gap > 2 mm. Soft tissue dimension changes, patient satisfaction, implant failure, prosthesis failure, and complications as secondary objectives will be examined. The null hypothesis is that xenografting may considerably reduce the recession of peri-implant tissue and increase patient satisfaction.

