### Secondary outcomes

Soft tissue changes: A periodontal probe and a stent put on the reference point will be used to assess soft tissue height changes in the mesial, middle, and distal regions of the buccal area of the implant site following implant placement at the surgical visit, 3 months, and 6 months after implant placement [3, 11]. Soft tissue thickness will be assessed at the 4 and 8 mm apically of the mid-buccal gingival margin. It may be done using an 15-endodontic file [11] at 2 weeks, 3 months, and 6 months after implant placement [11]Implant failure: Any implant removed after placement due to mobility, progressive marginal bone resorption, infection, or any mechanical complication during and after the surgery that cannot be forecasted before the procedure (e.g., implant fracture) [16, 17]Prosthetic failure: Any prosthesis which fails with the implant or cannot be placed in terms of implant failure or will be replaced for any reason [16]Biological or prosthetic complications [6]Subjective patient satisfaction of the surgical results: Patient satisfaction esthetically and financially after implant placement [7] will be measured applying three questions, functionally, esthetically, and undergoing a similar treatment again during 1 year of follow-up. It will be performed by possible answers for questions 1 and 2 are “yes, absolutely = 4,” “yes, partially = 3,” “don’t know = 2,” “rather not = 1,” and “Absolutely not = 0.” For question 3, “yes = 1” or “no = 0” [18]

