## Statistical analysis

Cohen’s *k* statistic will be used to measure consistency in descriptive data. Frequency numbers (absolute and relative values) and metric data are examples of descriptive statistics (arithmetic mean, standard deviation, and median). The intra-class correlation coefficient will be used to assess consistency between the two examiners for continuous data, such as clinical parameters. The enumerated data will be reported as percentages and the measured data as mean standard deviation or median (quartile spacing). The impact of changes in measurement time between the two study groups at two times (baseline and follow-up) will be compared using an analysis of variance (ANOVA), with the kind of intervention as a between-subject factor. The height and thickness of bone and soft tissue will be quantitative variables. Implant failure, prosthesis failure, comorbidities, and patient satisfaction will all be stated exclusively in terms of frequency (percentage). SPSS 25.0 will be used for all statistical analyses. The significance threshold is specified as 0.05.

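### The stated null hypothesis is the expected benefit of xenograft, and its patient satisfaction part has no planned between-arm comparison and two conflicting assessment times

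*Protocol article*

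**What the plan says.** Four places in the protocol article bear on this.

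- **Objective and hypothesis.** The hypothesis is "The null hypothesis is that xenografting may considerably reduce the recession of peri-implant tissue and increase patient satisfaction". The sentence before it gives satisfaction a secondary role: "Soft tissue dimension changes, patient satisfaction, implant failure, prosthesis failure, and complications as secondary objectives will be examined".
- **Statistical analysis.** Height and thickness of bone and soft tissue are compared by ANOVA at baseline and follow-up, with intervention as the between-subject factor and a significance level of 0.05. For the other outcomes: "Implant failure, prosthesis failure, comorbidities, and patient satisfaction will all be stated exclusively in terms of frequency (percentage").
- **Abstract, Method and design.** "Patients’ satisfaction, implant failure, prosthesis failure, and complications will be assessed as secondary outcomes after 6 months".
- **Secondary outcomes.** Satisfaction is measured by "three questions, functionally, esthetically, and undergoing a similar treatment again during 1 year of follow-up". Questions 1 and 2 are scored on five levels from 0 to 4; question 3 is yes or no.

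**The concern.** A null hypothesis is what a significance test may reject. Here the sentence labelled as the null is the result the investigators hope for. Taken at its word, a small p-value would count against the graft and a large one would leave the benefit standing. In a trial of 30 patients a non-significant result is quite possible, so the label should not be one under which benefit is retained by default. The sentence also sets no size for a considerable reduction, and it joins the primary outcome (bone) with secondary ones (soft tissue, satisfaction) in a single statement.

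Higher satisfaction is part of that hypothesis, yet the analysis section commits to percentages only. Both the abstract and the Discussion say that the patient-reported outcomes will help in choosing between treatments. Percentages from about 15 patients per arm, with no comparison or interval planned, support that use poorly. The reader also cannot tell when satisfaction is measured.

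**Working it through.** The point rests on wording, so the main check sets the passages side by side. Some arithmetic then shows what a satisfaction comparison could deliver.

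**1. Hypothesis against analysis**

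| Part of the hypothesis | Planned analysis | Between-arm test? |
|---|---|---|
| Less recession of bone and soft tissue | ANOVA, intervention as between-subject factor, level 0.05 | Yes; it tests no difference |
| Higher satisfaction | Frequencies and percentages only | No; excluded by wording |

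The ANOVA's null is equality of the groups, which is not the null that the Objective section states. For bone and soft tissue the mismatch lies in the label and changes no computed result. For satisfaction the mismatch is one of substance.

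**2. Timing**

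The abstract places satisfaction after 6 months. The Secondary outcomes section refers to one year of follow-up. Elsewhere in the text, the second CBCT and the last soft tissue measurement are at 6 months, and the abstract places failures and complications there too. No 12-month visit is described in the text shown.

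**3. What the trial was sized for**

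The Sample size section gives SD 1.2 mm, difference 1 mm, a paired t-test, a minimum of 12, and 15 per group for 20% dropout. Power is not stated; 80% is assumed here, with two-sided 0.05:

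- n = ((1.96 + 0.84) × 1.2 / 1)² = 11.3, rounded up to 12 (14 by the exact t-distribution)
- 12 / (1 − 0.20) = 15 per group

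The stated figure reproduces by the normal approximation. It concerns bone only; nothing was sized for satisfaction.

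**4. What a comparison of the yes/no item could show**

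The protocol gives no expected rates, so those below are assumptions. With n = 15 per arm and the mean of the two rates written p̄:

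Power ≈ Φ{ [ |p₁ − p₂| − 1.96 √(2p̄(1 − p̄)/n) ] / √[(p₁(1 − p₁) + p₂(1 − p₂))/n] }

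- 70% against 90%: (0.20 − 1.96 × 0.1461) / 0.1414 = −0.61, so power is about 27%. Fisher's exact test, by full enumeration, gives 15%.
- 50% against 90%: (0.40 − 1.96 × 0.1673) / 0.1506 = 0.48, so power is about 68%. Fisher's exact test gives 54%.

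For 70% against 90%, the approximate 95% interval for the difference has half-width 1.96 × 0.1414 = 0.28, or 28 percentage points. Dropout would widen it.

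**The case against.** The strongest reply is that this is a drafting slip with little effect. The planned ANOVA tests equality whatever the Objective section calls its null. The abstract and Discussion make the intended question clear, and no analyst would read a small p-value as evidence against the graft. This stands for bone and soft tissue. A reader might infer that the trial's whole hypothesis is untestable; the protocol does not support that, because the Statistical analysis section fixes a between-group analysis for those outcomes.

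A second reply is that descriptive reporting of a secondary outcome in 30 patients is reasonable, given the low power shown above. It is. But it does not fit a hypothesis that satisfaction rises. Nor can the gap be left to a separate analysis plan, since the word exclusively is a positive choice that a later test would contradict.

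A third reply is that the one-year phrase may belong to the wording of question 3, and that the flow chart and SPIRIT figure, which are not shown, may fix the visit. Either is possible, but the two text passages still need to agree.

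Two further inferences are tempting and fail. One is that satisfaction is specially free of assessment bias because patients are blinded: the Blinding section also hides allocation from the data assessor and the statisticians, and the Primary outcome section gives the radiographic examinations to an independent examiner. The other is that the arms would be assessed at different times: any looseness in timing applies equally to both randomized arms, and nothing suggests otherwise.

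**Conclusion.** The point holds in three limited parts: the null is mislabelled; satisfaction is hypothesised to increase but excluded from comparison; and its assessment time is given in two ways. The randomization and the primary bone analysis are untouched. What is lost is an answer to one stated secondary hypothesis and a clear statement of what a non-significant result means.

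Adding a comparison would not make the trial informative on satisfaction unless the difference were large. The power of 15% to 54% by Fisher's exact test rests on assumed rates, 15 analysed patients per arm and two-sided 0.05. That favours estimation with intervals and an exploratory label over any confirmatory claim. The correction is worth making because it is cheap, not because the main result depends on it.

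**What to change.** 1. State the primary null as no difference between arms in change in buccal bone dimensions, against a two-sided alternative. Add separate secondary nulls of no difference for soft tissue and, if it is kept, for satisfaction, each two-sided.
2. Make the abstract and the Secondary outcomes section agree on one satisfaction time point, the same for both arms; the existing 6-month visit is one option.
3. Then choose one of two courses.
   - Compare the arms at that time: Wilcoxon rank-sum for each of the two 0–4 items and Fisher's exact test for the yes/no item, with confidence intervals for the differences. Label these secondary and exploratory because of the low power, and remove the restriction to percentages for satisfaction.
   - Or delete satisfaction from the hypothesis and describe it as a descriptive outcome.

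The cost is a few sentences and at most three simple comparisons. No extra visit is needed if the 6-month visit is chosen and the questions are asked there. Recruitment began in December 2021, so the earliest patients would have reached 6 months by June 2022, before the article appeared. If questionnaires have already been given, the time point should be settled from when they were given, before anyone looks at results by arm.

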## Methods

### Overview

The initial research was planned as a randomized controlled trial. The goal was to enroll 30 patients who needed anterior maxillary teeth and first maxillary premolar dental replacements and evaluate the interventional impact before and after treatment between the intervention and control groups (Figs. 1 and 2). Patients referred to a private clinic and the Oral and Maxillofacial Surgery Department at the Islamic Azad University of Tehran, Iran, as well as a private clinic will be chosen. These two facilities will handle all procedures, follow-ups, and analyses. The Iranian Registry of Clinical Trials (Identifier No. IRCT20211119053106N1) and Open Science Framework (OSF) (Registration DOI 10.17605/OSF.IO/VUGFQ) have been notified about this project. The current study’s recruiting and treatment methodology were authorized by the Research Ethics Committee of the Islamic Azad University-Dental Branch, Tehran, Iran (IR.IAU.DENTAL.REC.1400.096). Before creating a treatment plan, researchers will assess each participant’s overall health and periodontal status. Consent to participate in the research is obtained when the patient’s clinical and periodontal health condition has been established.

**Fig. 1 Fig1:**
[figure not shown]
Flow chart of the treatment process. *W weeks. ^1^Using CBCT. ^2^Using an intraoral scanner

**Fig. 2 Fig2:**
[figure not shown]
SPIRIT figure

### Inclusion criteria

The inclusion criteria for this research are as follows:Patients need the extraction of a maxillary tooth (numbers 14–24) and the possibility of immediate placement of implants on the same siteIntact buccal bone [1, 2, 5]Gap space of more than 2 mm between the implant and buccal bone [3, 5]. Immediate implants, if possible, will be placed in the ideal three-dimensional position immediately after tooth extraction, considering the first stability and the possibility of immediate temporary prosthesis placement

### Exclusion criteria

The exclusion criteria for this research are as follows:The presence of periodontal diseaseThe presence of systemic or local diseases that may interfere with bone repair (including diabetes, osteoarthritis, hypothyroidism, hyperparathyroidism, and osteoporosis)Using drugs that prevent implant placement and interfere with osteointegration, or bone and gingival tissue repair (including bisphosphonates)PregnancyDrug addiction or smokingAcute infection at the implant sitePatient undergoing radiotherapyHaving parafunctional habits like bruxism or clenching [1, 4, 5]

Patients who fulfill these requirements will be excluded from the research. Selected individuals will have their teeth extracted and will get an implant as well as a temporary prosthesis right away.

### Allocation and randomization

#### Randomization

Each subject will be issued a numerical code that will be placed in a matching envelope that will be kept sealed until the procedure by external investigators. As a result, participants will be divided into two groups: group 1 (with bone graft) and group 2 (without bone graft). Using a web-based randomization service, an independent investigator will produce the randomized sequence (www.randomization.com). Balanced with a block size of 4, blocked randomization will be applied. Only after the implants have been implanted on the day of surgery will the surgeon open the sequentially numbered, sealed envelopes.

#### Blinding

It is impossible to blind the operator. The treatment assignment will be hidden from the data assessor. Furthermore, all patients will be unaware of which group they are in. Operators do not have access to statistical assessment tools due to the principle of blindness. Likewise, statisticians are unaware of treatments and groups.

## Intervention

### Extraction and implant

After extraction in the fresh socket, patients in group 1 (implant with bone graft) and group 2 (implant without bone graft) will receive implants with sandblasted, large grit, and acid-etched (S.L.A) implant surfaces (Implantium, Dentium, South Korea). Using a periotome and forceps, the target tooth is extracted atraumatically with a maximal effort to maintain the buccal plate without flap reflection.

In both groups, implants will be placed 3 mm measured with a millimeter-sized periodontal probe apically to the buccogingival edge of adjacent teeth. The gap width between the immediate implant surface and buccal bone will be measured after implant placement by a periodontal probe to ensure a space of more than 2 mm. Patients with a gap of <2 mm (healed spontaneously without any grafting procedure) will be excluded from the study [5]. After placing the implants, all participants will be divided into two groups: group 1 (implant with bone graft) and group 2 (implant without bone graft).

In patients allocated to group 1, the tooth socket area will be filled with xenograft (SigmaGraft, Fullerton, CA, USA) next to the implant surface after implant insertion. Group 2 will receive an immediate implant that does not need any bone graft material [6]. All surgical operations will be performed by [name]. [name], Oral and Maxillofacial Surgeon.

Prophylactic antibiotics consist of 2 g of oral amoxicillin capsules or 600 mg of oral clindamycin capsules given 1 h before surgery. With the flapless tooth extraction procedure, anesthesia including lidocaine and epinephrine 1/80,000 is injected into the tooth extraction region as infiltration and site preparation [3, 11].

All patients will get the healing abutment for about 2 weeks, once the fixture is installed. Antibiotics (amoxicillin 500mg/clindamycin 300mg) and analgesic (ibuprofen 400mg) will be used to relieve discomfort following implant surgery. The patient will be given chlorhexidine gluconate 0.12% oral rinse (every 12 h for 7 days) after-surgery instructions [3, 11].

We will remove the healing abutment and replace it with a laboratory-modified abutment and a temporary prosthesis that will be non-functional or out of occlusion when the sutures are removed, which is normally 2 weeks following implant placement. The temporary prosthesis will be used for 3 months after the implant is implanted in both groups, following which the permanent prosthesis will be used. To avoid biomechanical stresses from accessing the implant fixture and causing late recovery or treatment failure, the temporary prosthesis should not be functional. The patient will be excluded from the trial if they have parafunctional behaviors like bruxism or clenching [12, 13].

## Outcomes

### Primary outcome (buccal bone changes)

A radiologist will assess bone tissue using a CBCT radiograph created by PlanMeca in Finland in 2016 with the following specifications: voxel size 200 μm, FOV: 8 × 11, 90 kV, and 9 mAs, as well as Romexis measuring software. After the temporary prosthesis is in place, the first tomography examination will be performed. During the examination, a tomographic positioner will be used to standardize the results. To estimate the thickness of the bone at a buccolingual distance, tomographic sections are made such that a slice passes exactly through the center of the fixture. Measurements will be taken apically to the implant platform in the buccal lingual dimension of the slice at 1.5-mm, 3-mm, and 5-mm intervals [3, 5, 11, 14]. In a cross-sectional view and the center of the tooth site, bone height measurements from the buccal crest to the face of implants will be made using Romexis software [15]. Before the procedure, the distance between the buccal bone surface and the implant fixture (GAP) will be measured using a Periodontal Probe CP15 University of North Carolina, and 6 months afterwards by tomographic analysis [3]. All radiographic exams will be performed by an independent examiner [16].

Six months following surgery, a second computed tomography (CBCT) will be performed. With the same basic evaluation methods, the thickness of the bone at a buccolingual distance will be assessed.

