## Sample size

Using the PASS sample size program, the present research sample size was calculated (version 11.0). Paired sample t-test power analysis was used to estimate sample size. If the mean standard deviation of the changes in bone dimensions is 1.2mm and the difference in sizes is 1 mm on both sides, the minimum sample size is 12. The research starts with 15 samples for each group, with a 20% risk of sample dropout [3].

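### The primary outcome names no single primary variable among four analysed bone measures (five if the gap is tested), and the sample size is tied to none of them

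*Protocol article*

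**What the plan says.** The section Primary outcome (buccal bone changes) describes these measures under a single heading:

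- Thickness: "Measurements will be taken apically to the implant platform in the buccal lingual dimension of the slice at 1.5-mm, 3-mm, and 5-mm intervals". That makes three values per scan.
- Height: "bone height measurements from the buccal crest to the face of implants will be made using Romexis software".
- Gap: "the distance between the buccal bone surface and the implant fixture (GAP) will be measured using a Periodontal Probe", with a tomographic reading at 6 months.

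No level or measure is singled out, and no average or composite is defined. The closing paragraph, on the second scan, mentions thickness only.

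Sample size bases the calculation on this premise: "If the mean standard deviation of the changes in bone dimensions is 1.2mm and the difference in sizes is 1 mm on both sides". It does not say which dimension is meant. It gives a minimum of 12, raised to 15 per group for 20% dropout.

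Statistical analysis plans an ANOVA over two time points "with the kind of intervention as a between-subject factor". It lists what is analysed: "The height and thickness of bone and soft tissue will be quantitative variables". It then sets one threshold: "The significance threshold is specified as 0.05".

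Objective and hypothesis speaks only of dimensional change of the buccal bone. The abstract's Discussion and the main Discussion put the question in terms of vertical bone and gingival recession.

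**The concern.** A primary outcome should fix, before the data are seen, the one quantity on which the trial's main claim rests. Here three sections could have done so (outcome, sample size, analysis), and all three leave it open. As written, a significant difference at any one thickness level, or in height, could be reported as showing that xenograft preserves buccal bone. Nothing in the text marks that as a selected result. The error rate of the primary claim is then no longer the stated 0.05.

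The planning figures suffer too. A 1 mm difference and a 1.2 mm standard deviation cannot be judged for plausibility, or checked against the results, unless they belong to a named measure. Thickness at 1.5 mm, thickness at 5 mm and crest height need not share a standard deviation or an expected effect.

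**Working it through.** **Inputs from the protocol article.** Thickness at three levels, height and gap (Primary outcome). Difference 1 mm, standard deviation 1.2 mm, minimum 12, 20% dropout, 15 per group (Sample size). Threshold 0.05, with bone height and thickness as the analysed bone variables (Statistical analysis).

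**Assumed, because not stated.** Two-sided tests, 80% power, and an equal correlation r between every pair of measures, varied from 0 to 0.95.

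**Step 1: the plan's own figure.** The article says "Paired sample t-test power analysis was used to estimate sample size". The paired formula with the normal approximation gives n = (1.2 × (1.960 + 0.842) / 1)² = 11.3, rounded up to 12. Then 12 / (1 − 0.20) = 15. The stated figures reproduce (an exact paired t calculation gives 14 instead of 12). They do so with one generic standard deviation and one generic difference, so the calculation does not reveal which measure was meant.

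**Step 2: count the measures.**

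- Thickness only, as in the paragraph on the second scan: 3.
- Thickness and height, the bone variables listed under Statistical analysis: 3 + 1 = 4.
- With the gap as well, as described under Primary outcome: 5.

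**Step 3: false-positive rate if any one of k tests at 0.05 counts as success.** For independent tests the rate is 1 − 0.95^k:

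- k = 3: 14.3%
- k = 4: 18.5%
- k = 5: 22.6%

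For a common correlation r, with c = 1.96, the rate is

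1 − ∫ φ(u) [Φ((c − √r·u)/√(1−r)) − Φ((−c − √r·u)/√(1−r))]^k du.

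| Assumed r | 3 tests | 4 tests | 5 tests |
|---|---|---|---|
| 0 | 14.3% | 18.5% | 22.6% |
| 0.5 | 12.5% | 15.6% | 18.3% |
| 0.7 | 10.9% | 13.0% | 14.8% |
| 0.8 | 9.8% | 11.4% | 12.7% |
| 0.9 | 8.4% | 9.4% | 10.2% |
| 0.95 | 7.3% | 8.0% | 8.5% |

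Simulated two-sample t-tests agree. With 15 per group, four tests give 18.4% at r = 0 and about 9.5% at r = 0.9; five tests give 22.6% and 10.1%.

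**Step 4: splitting the threshold instead.** Bonferroni over five measures means 0.05 / 5 = 0.01 each; over four, 0.05 / 4 = 0.0125. Suppose the 1 mm and 1.2 mm figures applied to each measure. A two-group t-test with 12 per group would then have about 50% power at 0.05 and about 25% at 0.01. Splitting is therefore costly in a trial of this size, and naming one variable is not. (That the two-group power is only about 50% is a separate sample-size matter.)

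**The case against.** A reader might infer that there are five primary endpoints, each tested at 0.05, and that the error rate simply is 10% to 23%. The documents do not support that.

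- **The gap.** It serves as an eligibility check (Inclusion criteria; Extraction and implant) and is not among the variables listed under Statistical analysis. No sentence says it will be compared between groups. This stands: four is the better-supported count, and five is conditional.
- **Separate tests.** The article does not say that each level gets its own ANOVA, or that one significant result suffices for primary success. This also stands: the rates in the table are conditional on both. But nothing in the text rules either out.
- **The correlation.** It appears nowhere in the documents. Independence is a ceiling and is implausible for levels read from one central slice. The lower end has no natural stop at 0.9; at 0.95 the rates are 8.0% for four tests and 8.5% for five.
- **Multiplicity rules.** An adjustment method may sit in an analysis plan that is not shown, so its absence here is no fault. The identity of the primary variable is different. It is core protocol content, which the article addresses in three sections without settling.
- **Which variable.** Making averaged thickness primary would set aside the vertical-bone question posed in the abstract and the Discussion. That choice belongs to the investigators.

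**Conclusion.** The concern holds in conditional form. The primary outcome names no single variable among four analysed bone measures (five if the gap is tested), and the sample size is tied to none of them. That much rests on the text alone.

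The size of the consequence rests on three assumptions: each measure is tested at a two-sided 0.05, any one success counts, and the correlation lies between 0 and 0.9. Under these the false-positive rate for the primary claim is 9.4% to 18.5% with four tests and 10.2% to 22.6% with five. On the narrowest reading, thickness alone, it is 8.4% to 14.3%. Higher correlations bring it closer to 5%, but every case computed stays above it. The point should be settled, and doing so needs no extra patients or measurements.

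**What to change.** Before group results are seen, issue a dated amendment and update both registry entries so that they:

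1. Name one primary variable and one between-group contrast at 6 months, tested at 0.05. Two candidates fit the article. One is buccal thickness averaged over the 1.5, 3 and 5 mm levels, estimated in one model with level as a within-patient factor. The other is crest height, which matches the vertical-bone aim in the abstract and the Discussion. The investigators choose.
2. Tie the 1 mm difference and the 1.2 mm standard deviation to that variable, or replace them with figures that belong to it. For averaged thickness, the standard deviation follows from the single-level value as 1.2 × √((1 + 2r)/3). That is 0.98 mm at r = 0.5 and 1.16 mm at r = 0.9, if 1.2 mm applies to each level.
3. Report the remaining bone measures, including single levels and the gap if it is compared, as secondary with 95% confidence intervals and no confirmatory claim.

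**Cost.** The wording is about a paragraph, but the trial is registered in two places, ethics-approved and recruiting since 6 December 2021, so the change must be documented and dated. A significant result on a single non-primary level or measure can no longer be claimed as primary success. Whichever of thickness and height is not chosen becomes secondary.
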